- **Study Protocol**
- **Effectiveness of Reciproc system for anterior teeth with apical periodontitis: a randomized controlled pragmatic trial**
- **Proponent:**
- PhD Student: [name]
- Health Sciences Graduate Program
- Federal University of Sergipe
- **Doctoral Adviser:**
- [name]. [name]
- Department of Dentistry
- Health Campus / Biology and Health Science Center
- Federal University of Sergipe
- Aracaju
- June 2015
- **ABSTRACT**
- Single file canal preparation techniques emerged in an attempt to overcome drawbacks related to manual and continuous rotary techniques. It has shown promising results in in-vitro studies, but its effectiveness has not yet been tested in clinical studies. Hence, this proposal seeks to investigate, through an equivalency randomized controlled clinical trial, the effectiveness of the Reciproc® single file, single cone system, regarding its success rate, incidence rate of post-operative pain and PAI score changes. This trial will follow the Consort guidelines, having a parallel design and using an active treatment as control – the crown-down instrumentation technique and the lateral condensation obturation technique. Patients in need of endodontic treatment for anterior teeth due to pulp necrosis and with radiographic evidence of apical periodontitis will be randomized to receive endodontic treatment either by the Reciproc® single file, single cone system or by the crown-down manual technique with stainless steel files. Patients will be questioned about their pain levels at baseline and then 24 hours, 72 hours days and 7 days after treatment is performed. The Wilcoxon test will be used to compare treatment pain scores. Patients will be called for one- year follow-up visits in which PAI score changes and clinical signs of periapical pathosis will be ascertained. Data related to PAI scores will be submitted to the Wilcoxon test to compare treatment outcomes and to the Man-Whitney test to compare one-year follow-up scores within each treatment group. Each individual treatment will be classified as “success” if their PAI scores are 2 or lower and they show no clinical signs or symptoms of periapical disease. Success rates of each treatment and the relative risk of experimental group in relation to control will be determined. In addition, Fishers exact test will be used to compare treatment groups’ success rates. For all analyses, a 95% significance level will be used.

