- A decrease in treatment time may enable a reduction in the cost of treatment, while increasing the productivity of public and private clinics. In addition, it also enhances ergonomics and makes the experience of root canal treatment less uncomfortable for patients. Despite these advantages, faster root canal preparation techniques must not compromise the short and long-term outcomes of root canal treatment. The reciprocating single file philosophy was developed to reduce and simplify root canal treatment time. If its clinical performance is similar or better than the performance of other root canal preparation techniques, it will enhance services delivered to the public, reducing costs and enhancing productivity. Hence, it is important to investigate the clinical performance of endodontic techniques that make use of reciprocating single file root canal preparation in order to help private and public endodontic treatment providers to chose and manage their practice.
- **3. Research Objectives**
- 3.1- General objective
- To evaluate the clinical effectiveness of the Reciproc reciprocating single file system in regards to the treatment of anterior teeth with apical periodontitis
- 3.2. – Specific objectives

1. Compare mean periapical index score (PAI) score changes between reciprocating single file and hand file instrumentation of root canals;
2. Compare the success rate of treatments performed with reciprocating single file and hand file instrumentation of root canals;
3. Compare the incidence and severity of postoperative pain between the two instrumentation modalities;
4. Compare the incidence of flair-up between the two instrumentation modalities

- **4. Goals**

1. Contribute to enhance the scientific knowledge related to the preparation and obturation of root canals with reciprocating single files and the single cone technique, respectively.
2. Contribute to enhance the quality of care offered by public clinics in which endodontic treatment is performed
3. Improve the quality of dentistry-related clinical trials of the post graduate program in Health Sciences of the Federal University of Sergipe, Brazil, considering that these are at the top of the scientific evidence pyramid and, hence, promote evidence based dentistry.
4. Establish partnership with other institutions for the design and execution of multicenter randomized clinical trials;

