5. Enhance the quality of education provided to students of the graduate program in Health Sciences of the Federal University of Sergipe;
6. Produce a doctoral thesis and at least two original research articles to be published in journals with an impact factor of 2 or more.
7. **Methodology**

- 5.1 Experimental Design
- This study will be a randomized controlled pragmatic clinical trial, which will follow the CONSORT (<http://www.consort-statement.org/>) statement guidelines. It will have a two-arm, parallel design (1:1 allocation ratio equivalency). The endodontic treatments to be performed are either a combination of a single-file and single-cone (SFSC) technique using the Reciproc system (experimental group) or an association of the crown-down hand files with the lateral compaction obturation (HFLC) technique (control group). The main outcome of interest is mean periapical index score (PAI) (19) difference between the two groups 12 months after treatment. Peak of pain during the first 24 hours after treatment and postoperative pain 24, 48 hours and 7 days after treatment are the secondary outcomes.
- The trial will be based on the following PICO question:
- P (Population): patients above 18 years of age, who are scheduled for an endodontic treatment in one of the public services where the study was performed cities (i.e., Capela, Estância, Laranjeiras and Nossa Senhora do Socorro) located in the state of Sergipe (Brazil), with anterior teeth presenting pulp necrosis and radiographic evidence of apical periodontitis (symptomatic apical periodontitis, asymptomatic apical periodontitis, and chronic apical abscess) with a diameter greater than 2 mm.
- I (Intervention): A combination of a reciprocating single-file and single-cone technique using the Reciproc system.
- C (Control): An association of the crown-down technique hand files with the lateral compaction obturation technique.
- O (Outcomes): Mean PAI difference between the intervention and the control group 12 months after treatment.

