- Therefore, the research question is the following: For patients presenting anterior teeth with pulp necrosis and apical periodontitis, is there difference in the outcomes obtained with hand file instrumentation and lateral compaction obturation compared with the outcomes obtained with reciprocating single file instrumentation and single cone obturation, concerning the healing of periapical lesions and postoperative pain incidence and severity? The hypothesis to be tested is that using reciprocating single files instrumentation and single cone obturation has similar effectiveness treating apical periodontitis as hand file instrumentation and lateral compaction obturation technique. In addition, the hypothesis that both endodontic protocols result in the same incidence and severity of postoperative pain and flair-up will also be tested.
- 5.2 Method
- 5.2.1 Sample Size Calculation
- The sample size was calculated for the main outcome, defined as the mean periapical index score (PAI) difference between protocols of the apical lesion 1 year after treatment. The calculation for similarity trial used an equivalence limit of 0.5, a standard deviation of 0.74 (20), type I error of 0.05, and a power test of 0.90. Furthermore, the sample was increased by 20% to compensate for any drop-out. This resulted in 60 teeth per experimental condition.
- 5.2.2 Recruitment and eligibility criteria
- The recruited participants will be patients who are scheduled for an endodontic treatment in one of the public services where the study will take place. Patients with anterior teeth presenting pulp necrosis and radiographic evidence of apical periodontitis (symptomatic apical periodontitis, asymptomatic apical periodontitis, and chronic apical abscess) with a diameter greater than 2 mm will be invited to participate in the study. Those who agreed to participate and sign the informed consent (appendix I) form will be included in this study. Only one tooth per participant will be included in the trial. Teeth with an immature apex, any radiographic evidence of root resorption, previously treated root canal or requiring extensive prosthetic rehabilitation will be excluded. Participants presenting a pre-existing health or oral condition that placed them at risk during the trial, as well as those having generalized periodontal disease, and women who are pregnant or breastfeeding are also going to be excluded.
- 5.2.3 Baseline evaluation

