- To evaluate participants’, the pupal condition will be evaluated through thermal sensitivity tests – cold and heat – and through periapical radiographs made by the paralleling technique. A clinical evaluation will also be performed (visual inspection, palpation, vertical and horizontal percussion) to identify and register the presence or absence of sinus tract, tenderness, tooth mobility and pain.
- If the occurrence of pulpal necrosis and apical periodontitis is confirmed and if the patient gives written consent to participate in the study, the baseline PAI will be recorded according with the instructions of Orstavick et al (19).
- Table 1. Periapical Index Score (19).

| - PAI SCORE | - Criteria |
| --- | --- |
| - 1 | - Normal Periapical structures |
| - 2 | - Small changes in bone structure |
| - 3 | - Changes in bone structure with some mineral loss |
| - 4 | - Periodontitis with well-defined radiolucent area |
| - 5 | - Severe periodontitis |

- In case the patient reports any sensitivity before treatment, its level will be registered according to the verbal scale detailed in table 2. If the patient does not report any pain, the score 0 will be registered, which corresponds to absence of pain.
- Table 2. Verbal pain scale (21).

| - 5-Level pain scale to evaluate pain severity: Reference Values given to patients | | |
| --- | --- | --- |
| - 0 | - No pain | - The patient feels good |
| - 1 | - Mild pain | - If distracted, he/she does not fell pain |
| - 2 | - Moderate Pain | - The patient feels moderate pain, even when concentrating on some activity |
| - 3 | - Considerable | - The patients feel very unwell but nevertheless can continue with ordinary activities of daily life |
| - 4 | - Severe pain | - The patient is forced to give up ordinary activities of daily life |
| - 5 | - Extreme | - The patient is no longer able to perform any type of activity and needs to lie down and rest |

- 5.2.4 Random sequence generation and allocation concealment
- A random list will be created using the website [www.sealedenvelope.com](http://www.sealedenvelope.com/). The treatment to be performed on each patient will be placed into opaque and sealed envelopes by a third party not involved in the study intervention. The dentists who will perform the clinical procedures will only open the envelope at the moment of the intervention.
- 5.2.5 Study interventions

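### The primary 12-month PAI comparison makes no use of the recorded baseline PAI, and objective 1 and the abstract speak of PAI change, for which 5.3 names no mean-change analysis

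*Protocol*

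**What the plan says.** Four places in the protocol identify the main outcome, and they agree.

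- Section 5.1: "The main outcome of interest is mean periapical index score (PAI) (19) difference between the two groups 12 months after treatment".
- The PICO item in 5.1: "Mean PAI difference between the intervention and the control group 12 months after treatment".
- Section 5.2.1: "The sample size was calculated for the main outcome, defined as the mean periapical index score (PAI) difference between protocols", taken 1 year after treatment.
- Section 5.3 attaches the main-outcome label to the 12-month comparison. It is tested by a Wilcoxon rank-sum TOST, with the 95% confidence interval for the mean PAI difference required to lie inside the equivalence limit.

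Two places speak of change instead. The first specific objective in 3.2 is: "Compare mean periapical index score (PAI) score changes between reciprocating single file and hand file instrumentation of root canals". The abstract describes effectiveness "regarding its success rate, incidence rate of post-operative pain and PAI score changes". Neither calls change the main outcome.

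Section 5.2.3 says that, once eligibility and consent are confirmed, "the baseline PAI will be recorded". Baseline PAI then has two stated uses. It helps to classify teeth as healing (5.2.8, Evaluations), and PAI is compared between arms as a baseline characteristic (5.3). It does not enter the primary test.

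**The concern.** There are two linked issues.

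First, objective 1 has no matching analysis. Section 5.3 tests the 12-month score and, separately, the association of treatment with categories of periapical status, but never mean change. Score and change have different variances, and in any one trial their estimates differ by exactly the baseline imbalance between arms. A report written to objective 1 could therefore give a different number from one written to 5.1.

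Second, a baseline measurement of the outcome itself is collected on every tooth and left out of the primary comparison. The chosen test cannot take a covariate. It also does not itself deliver the quantity that 5.3 judges: the interval usually attached to a rank-sum test is for a location shift, whereas 5.3 sets an interval for a mean difference against 0.5.

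What is at stake is precision, and a clear link between objective, estimate and decision rule. The validity of the trial is not at stake.

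**Working it through.** **Inputs.** From 5.2.1: margin 0.5, SD 0.74, type I error 0.05, power 0.90, 20% allowance for drop-out, 60 teeth per arm. From 5.3: decision by a 95% interval. Assumed, because the protocol gives no figure: the correlation r between baseline and 12-month PAI (range 0.1 to 0.5), and that 0.74 is the SD of the 12-month score. Section 5.2.1 does not say whether 0.74 refers to the score or to the change. All power figures use the normal approximation with a true difference of zero.

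**Reproducing the sample size.** n per arm = 2 × [SD × (z(1−α) + z(1−β/2)) / margin]².

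- α = 0.05 per side: 2 × [0.74 × (1.645 + 1.645) / 0.5]² = 47.4, so 48. Then 48 / 0.8 = 60, which matches the protocol.
- α = 0.025 per side, as a 95% interval implies: 2 × [0.74 × (1.960 + 1.645) / 0.5]² = 56.9, so 57. Then 57 / 0.8 gives 72, which does not match.

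The trial was therefore sized for 0.05 per side (a 90% interval), without baseline adjustment.

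**Unadjusted power, 48 per arm.** SE = 0.74 × √(2/48) = 0.151, and power = 2Φ(0.5/SE − z(1−α)) − 1.

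- 90% interval: 2Φ(3.310 − 1.645) − 1 = 0.904.
- 95% interval: 2Φ(3.310 − 1.960) − 1 = 0.823.

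**Effect of baseline adjustment.** Adjusted SD = 0.74 × √(1 − r²). Unadjusted change SD = 0.74 × √(2(1 − r)) if the baseline SD is also 0.74.

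| r | Adjusted SD | Adjusted power, 95% CI | Adjusted power, 90% CI | Change SD | Raw change power, 95% CI | Raw change power, 90% CI |
|---|---|---|---|---|---|---|
| 0.1 | 0.736 | 0.828 | 0.907 | 0.993 | 0.388 | 0.589 |
| 0.2 | 0.725 | 0.844 | 0.917 | 0.936 | 0.489 | 0.669 |
| 0.3 | 0.706 | 0.869 | 0.932 | 0.876 | 0.598 | 0.751 |
| 0.4 | 0.678 | 0.901 | 0.951 | 0.811 | 0.712 | 0.831 |
| 0.5 | 0.641 | 0.937 | 0.970 | 0.740 | 0.823 | 0.904 |

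The correlation at which adjustment restores 0.90 under the 95% rule is √(1 − 48/56.93) = 0.396, so about 0.4.

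The raw-change columns depend on the equal-SD assumption. With a baseline SD of 0.4 and r = 0.3, the change SD is √(0.74² + 0.4² − 2 × 0.3 × 0.74 × 0.4) = 0.728, and the penalty disappears. If 0.74 is already the SD of the change, these columns do not apply.

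**How far score and change can differ in one trial.** With a baseline SD of 0.74, the SE of the baseline imbalance is also 0.151, so a one-SE imbalance separates the two estimates by 0.15. Under the 95% rule the half-width is 1.960 × 0.151 = 0.30, and the estimate must lie within about ±0.20 to conclude equivalence.

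**Why adjustment settles the wording.** If 12-month PAI = a + b × treatment + c × baseline + error, subtracting baseline from both sides gives change = a + b × treatment + (c − 1) × baseline + error. The coefficient b, its standard error and its interval are identical.

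**The case against.** A reader might infer that the protocol defines its primary outcome twice. It does not. Every place that names a main outcome gives the 12-month difference, and change appears only in an unranked objective and in the abstract. Under randomisation the two contrasts also have the same expected value. This part of the objection stands, and what is left is a mismatch of wording and a missing analysis for objective 1.

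A reader might also infer that omitting baseline PAI is an error, or that a chance imbalance passes in full into the result. An unadjusted comparison is valid in a randomised trial, and its interval already allows for chance imbalance. Only the regression slope times the imbalance carries over: with equal SDs and r = 0.3, an imbalance of 0.2 moves the 12-month contrast by about 0.06.

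The most tempting inference is that ignoring baseline leaves the trial underpowered. The stated inputs deliver 0.904 without adjustment at the alpha used for sizing. The fall to 0.823 arises from reading a 95% interval on a sample sized at 0.05 per side. The correlation may also be low, because entry is limited to apical periodontitis with lesions over 2 mm, which narrows the range of baseline PAI.

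Three endodontists treat patients at services in four cities, and the primary test ignores operator. The documents give nothing from which to size that effect, so it supports no more than an optional model term.

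A separate statistical analysis plan may exist. That does not remove the point, because 5.3 itself fixes a primary test that takes no covariate.

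**Conclusion.** The point holds as lost efficiency plus a mismatch between objective 1 and the main outcome. It does not invalidate the planned analysis. With 48 evaluable teeth per arm and 0.74 as the SD of the 12-month score, adjustment adds 0.5 to 11.4 percentage points of power under the 95% rule and 0.3 to 6.6 points under a 90% interval, for r from 0.1 to 0.5. If r is 0.2 or less, the gain is at most about 2 points under either rule. Adjustment offsets the separate alpha/interval mismatch only if r is about 0.4 or more, so it should not be relied on to cure it.

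The case for the change does not rest on power alone. A linear model gives directly the interval for a mean difference that 5.3 requires, and it makes the choice between score and change immaterial to the treatment estimate. The change is worth making, though the trial does not depend on it.

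**What to change.** - Replace the primary test in 5.3 with a prespecified linear model of 12-month PAI on treatment and baseline PAI, with robust standard errors. Operator may be added as an optional term.
- Read the confidence interval for the treatment coefficient against ±0.5, and state its level so that it agrees with the alpha used in 5.2.1.
- Keep the rank-sum TOST as a sensitivity analysis.
- Reword objective 1 and the abstract to refer to PAI at 12 months.
- State in 5.2.1 whether 0.74 is the SD of the 12-month score or of the change.

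The cost is protocol wording and one model, with no new data; the degrees of freedom spent are negligible at about 96 evaluable teeth. The one real downside is that the primary method itself changes, to a linear model on a five-level ordinal score. The robust standard errors and the retained rank-sum analysis are there to address that.

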- The participants allocated to the experimental intervention group will have their treatment performed by root canal preparation with reciprocating single file (Reciproc system) and obturated with the single cone obturation technique (SFSC group). Participants allocated to experimental control group will have their teeth treated by the crown-down instrumentation technique and the lateral compaction obturation technique (HFLC group).
- 5.2.6 Treatment protocol
- The endodontic treatments will be performed by three endodontists with more than 5 years of clinical experience. After the administration of local anesthesia and the placement of a rubber dam, the carious lesion will be removed and the access cavity performed. All endodontic treatments will be performed in a single session according to the randomization procedure.
- HFLC technique: The glide path will be established with stainless steel hand K-files up to a size #15. Then, the crown-down technique will be performed, initially with Gates-Glidden burs, which are to be used in a step-down manner to enlarge the orifice, prepare the cervical and middle-thirds of the canal, and provide straight-line access to its apical third. The apical foramen will be located by using an electronic apex locator (RomiApex A-15 Romidan, Kiryat Ono, Israel), and the working length established 1.0 mm short of its “0.0” reading. Apical preparation will be performed using ISO stainless steel hand files (Dentsply Sirona Endodontics, Ballaigues, Switzerland), starting with the selection of the first file to bind at the working length. The final instrumentation file will be set at 3 sizes larger than the first file used. The lateral compaction obturation technique will be used to fill the canals. A .02 taper gutta-percha cone will be selected according to the master apical file and then prefitted into the canal at the working length. After the canal is dried with paper points (Dentsply Sirona Endodontics), the master cone will be lightly coated with an epoxy resin-based sealer (AH Plus, Dentsply DeTrey, Konstanz, Germany) and placed into the canal down to the working length. Lateral compaction will be performed with finger spreaders (Dentsply Sirona Endodontics) and accessory cones (Dentsply Sirona Endodontics) chosen according to the final root canal dimensions. The excess filling material will be removed with a heated instrument and the access cavity sealed with glass-ionomer.

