- Baseline demographic data of the participants and clinical characteristics of the teeth included in the study will be categorized, and the absolute and relative frequencies calculated (except for PAI scores, final preparation size scores, age and follow-up time). The difference between the interventions regarding the distribution of these characteristics will be assessed by Chi-squared analysis. For PAI scores, final preparation size scores, age and follow-up time, data will be analyzed using either t-test or Mann-Whitney Rank-Sum test.
- The Wilcoxon Rank-Sum test for equivalence using two one-sided tests (TOST) procedure will be used to assess if, 12 months after the treatment, the 95% confidence intervals of the mean PAI score treatment difference falls within the pre-established equivalence limit (main outcome of interest). For all other outcomes, traditional two-sided superiority analyses will be used. The association between treatment protocol and changes on periapical status will be analyzed by Chi-squared test or by Fisher`s exact test. The success rates for each treatment protocol will be calculated, and differences analyzed by Chi-squared testing. Univariate logistic regression will used to determine any association between explanatory variables and the treatment’s success rate. Factors with a p-value < 0.1 will be included in a multivariate analysis. Odds ratios and 95% confidence intervals will be calculated.
- For all VAS data, normal distribution and possible differences between the treatments will be assessed through the Shapiro-Wilk test and t-test, respectively. Data from VRS will be analyzed through the Wilcoxon rank-sum test. The incidence of postoperative pain and flare-up will be calculated, and Chi-squared tests will be used to assess any possible association between treatment and incidence. Differences between the treatments regarding the incidence and intensity of postoperative pain will be calculated, as well as their confidence intervals at 95%. The level of significance will be set at 95% for all analyses.
- .
- **6. Scientific contributions of the proposal**

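### Operator is used neither in the random list nor in the primary equivalence test, although three endodontists deliver both techniques: valid, but some precision is given up

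*Protocol*

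**What the plan says.** Section 5.2.4 describes how the sequence is made: "A random list will be created using the website", with assignments put into opaque sealed envelopes by a third party. It adds that "The dentists who will perform the clinical procedures will only open the envelope at the moment of the intervention". It mentions no strata, no blocks and no separate envelope sets.

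Section 5.2.6 states that "The endodontic treatments will be performed by three endodontists with more than 5 years of clinical experience". Section 5.1 places the trial in four public services ("Capela, Estância, Laranjeiras and Nossa Senhora do Socorro") and describes a "two-arm, parallel design (1:1 allocation ratio equivalency" trial. The protocol does not say how the operators are spread over the services.

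Section 5.3 fixes the primary analysis: "The Wilcoxon Rank-Sum test for equivalence using two one-sided tests (TOST) procedure will be used", with equivalence concluded if "the 95% confidence intervals of the mean PAI score treatment difference falls within the pre-established equivalence limit". This is a pooled comparison of two samples. The only regression in the section is a logistic model for treatment success, with explanatory variables that are not listed.

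**The concern.** Both treatments are manual procedures. Section 5.2.6 leaves several steps to the operator's judgement and hand, such as choosing the first binding file, selecting accessory cones and controlling the pecking motion. Outcomes may therefore differ between operators.

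Operator is known before the envelope is opened, so it can be used at allocation and again in the analysis. The plan as written does neither. Nothing keeps each operator's patients evenly split between arms, and any difference between operators stays in the error of the primary comparison. What is at stake is precision in a trial whose conclusion depends on a confidence interval fitting inside a margin of 0.5 PAI points.

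**Working it through.** **Inputs from the protocol.** Margin 0.5, SD 0.74, type I error 0.05, power 0.90, 20% drop-out and 60 teeth per arm (section 5.2.1); three operators (5.2.6); 95% interval (5.3).

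**Assumptions.** Operators treat equal numbers. Operator explains a share R² of PAI variance, taken as 2%, 5% or 10%, because the protocol gives no figure. Normal theory stands in for the rank test, and the true difference is zero.

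**1. Reproducing the sample size.** For two one-sided tests at 0.05 each, with beta 0.10 split over the two sides:

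n = 2 × [0.74 × (1.645 + 1.645) / 0.5]² = 47.4, so 48 per arm; 48 / 0.8 = 60.

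The stated 60 is reproduced on a 90% interval basis. The protocol does not give its formula. A one-sided 0.025 with undivided beta gives 47, then 59, which is close but not exact.

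**2. How uneven can the split be?** With 120 patients, 60:60 overall and 40 per operator, the chance that at least one operator has a split of 24:16 or worse is about 36%. For 25:15 or worse it is about 19%.

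**3. What does imbalance do to the estimate?** With 48 completers per arm, the shift due to operator has mean 0 and SD = 0.74 × √R² × √(2/48). This gives 0.021, 0.034 and 0.048 for R² of 2%, 5% and 10%. In simulation (10,000 runs for each value), 95% of shifts lay within 0.04, 0.07 and 0.10.

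This is not added to the usual standard error. It is already part of it. At R² = 10%, 0.0478² + 0.1433² = 0.0228 = 0.1511², where 0.1511 = 0.74 × √(2/48) is the unadjusted standard error and 0.1433 the within-operator one. Simulated type I error at the margin was 4.6% to 5.4%, with or without adjustment.

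**4. What would using operator gain?** SE = 0.74 × √(1 − R²) × √(2/48); power = 2Φ(0.5/SE − z) − 1, with z = 1.645 for the 90% interval and 1.960 for the 95% interval.

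| R² | SE | Power, 90% interval | Power, 95% interval |
|---|---|---|---|
| 0 (unadjusted) | 0.151 | 90.4% | 82.3% |
| 2% | 0.150 | 91.1% | 83.4% |
| 5% | 0.147 | 92.0% | 84.9% |
| 10% | 0.143 | 93.5% | 87.4% |

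The gains are 0.7, 1.6 and 3.1 points on the 90% basis, and 1.1, 2.6 and 5.1 points on the 95% rule. With 50 evaluable per arm and t quantiles, the 95% rule gives 83.7% unadjusted, 86.2% at 5% and 88.5% at 10%.

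**5. Adjustment alone, with the list left unstratified.** The table assumes arms balanced within operator. The simulation kept the unstratified list and adjusted only the analysis (90% interval). Power went from 90.1% to 90.1% at R² = 2%, from 90.6% to 91.4% at 5%, and from 89.7% to 92.0% at 10%. The Monte Carlo error of each figure is about √(0.9 × 0.1 / 10,000) = 0.3 points.

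**The case against.** The strongest reply is that randomisation with an unadjusted comparison of 120 patients is valid as it stands. Each operator can deliver either arm, so no operator is tied to one treatment, and chance imbalance is sampling error that the interval already covers. If the SD of 0.74 is a total SD, it already contains between-operator variation, and the planned power is not eroded. All of this stands.

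The operator effect is also pure assumption. At R² = 10% with evenly spaced operators, best and worst would differ by 0.57 PAI points, more than the margin. The protocol works against large differences: operators have more than five years of experience, techniques are set out step by step, films are processed by a fixed time and temperature method, film position is standardised, and two blinded readers are calibrated to kappa above 0.80. This argues for the lower part of the range.

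The absence of stratification is inferred from silence. That is fair, but section 5.2.4 is where strata would be named, and allocation cannot be repaired after enrolment. Covariates may be left to an analysis plan that is not shown, yet section 5.3 already names the primary test, and that test has no operator term.

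A reader might infer three stronger things, none of which the protocol supports:

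- That operator imbalance biases the treatment difference. Its expected value is zero.
- That the trial could not show results by operator. They can be tabulated under the present list.
- That operator accounts for power being below 90% under the 95% rule. That shortfall comes from pairing a 95% interval with a size that matches a 90% interval, which is a separate and larger matter.

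**Conclusion.** The point holds as a modest loss of efficiency, not as a fault of validity. The plan describes one list without stratification and fixes a primary test that ignores operator, so chance operator imbalance remains in the contrast and some precision is given up if operators differ.

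For an assumed operator share of 2% to 10% of PAI variance, the standard error is about 1% to 5% larger than it need be. The gain available is roughly 1 to 5 power points under the stated 95% rule and about 0 to 3 on the 90% basis. If operators do not differ, nothing is gained. The case for acting is that the change is cheap. The point is confined to operator because the protocol does not say how operators map to services.

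**What to change.** In section 5.2.4, generate the list stratified by operator, with randomly varying block sizes that are not disclosed to the operators, and issue each operator a separate, sequentially numbered envelope set. At the least, state whether the list is stratified or blocked.

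In section 5.3, carry the equivalence test on an operator-adjusted difference in 12-month mean PAI, from a linear model with operator as a factor. This keeps the estimate on the scale on which the margin is set. An operator-stratified rank method is an alternative. A plain rank-sum test cannot take a factor, so the named primary method has to change. Tabulate the treatment difference by operator descriptively.

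No extra patients or visits are needed. The costs are three envelope sets instead of one, two degrees of freedom, and some predictability from blocking, because operators are unblinded and know past allocations. Varying the block sizes limits this. If it is still unacceptable, adjust the analysis only. When operators differ appreciably, that alone secures much of the gain: about 2.3 of 3.1 points at R² = 10% and about 0.8 of 1.6 at 5% on the 90% basis, subject to simulation error, and nothing measurable at 2%.
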